### Objectives and hypotheses

The objective is to determine if and how a mobile health system (mHealthApp), supported by data-driven Clinical Decision Support System (CDSS), both developed within the project PERSIST [22], will positively affect the behavior of survivors of breast cancer and colorectal cancer. The PERSIST intervention is expected to increase survivors’ self-efficacy and satisfaction with care as well as to reduce psychological stress for a better management of the consequences of cancer and its treatment. Intervention should result in an improved health outcomes and well-being. It should also re-integrate survivors into the labor market faster. By delivering prediction models from Big Health Data and a tool to support decision-making, PERSIST will enable clinicians to make optimal treatment decisions that have a positive impact on the survivor’s quality of life and health. The improved information and evidence will increase the effectiveness in cancer treatment and follow-up, i.e. effectiveness of management, intervention and prevention policies/strategies in order to respond quickly to the side effects and, if possible, avoid secondary diseases and fatal events, compared to regular routine. The long-term result is expected to reduce the socio-economic burden related to cancer survivors’ care.

The primary clinical objective is to assess the acceptability and usability of the mHealthApp and its impact on perceived self-efficacy and satisfaction with care from the perspective of the survivor. To evaluate the primary objective, two validated tools measuring self-efficacy can be utilized, Communication and Attitudinal Self-Efficacy scale for cancer (CASE-cancer) [23] and Strengths Self-Efficacy Scale (SSES) [24]. CASE-cancer was chosen since self-efficacy has been shown to be a protective effect for survivors who have higher perceived risk of recurrence [25–27]. Indivduals who are at higher risk with respect to health and well-being indicators may benefit more from the digital intervention.

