The secondary clinical objectives include measuring the patient activation and acceptance of the mHealthApp and experience of its use among them. Patient activation represents the knowledge, skills, and confidence to manage one's health. In multiple chronic conditions, it has been shown to contribute to improved self‐management behaviors [28, 29]. More active patients are more likely to believe their treatment plans reflect their values, more likely to face side effects, and more likely to initiate a healthier diet after diagnosis than less active patients [30]. Less active patients are less likely to understand their diagnosis, follow treatment regimens, and be satisfied with their care. System Usability Scale (SUS) [31], and User Experience Questionnaire (UEQ) [32] will be used to assess acceptance, user experience and possible issues regarding the use of mHealth App. Factors with significant impact on behavioral intention and motivation of use of mHealth Apps are perceived usefulness and ease of use, perceived risk and trust, the subjective norm and attitude [33]. Perceived ease of use is especially significant factor for middle-aged and older survivors.

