#### Primary and secondary endpoints

The primary endpoint is defined as: *increased perceived self-efficacy in participants (80 colorectal, 80 breast cancer survivors from the 4 pilot hospitals) following the mHealthApp supported intervention as measured using CASE-cancer scale for cancer as the validated standardized measure.*

The secondary endpoints include:observing modifications in patient activation levels measured using the PAM,observing modification in User acceptance depending on the level of support measured via SUS and UEQ,description of negative outcomes over time: hospitalization, exacerbations, treatment adherence, depression, recurrence, drug escalation,impact of variable modes of delivery (e.g., conversational agent) on quality of answers measure with DQS,the impact of patient trajectories (extracted from retrospective data) and PGHD on prediction of possible secondary disease or negative outcome,the impact of patient trajectories (extracted from retrospective data) and PGDH on improved intervention against the appearance of secondary diseases, worsening late toxicities or development of fatal events (sudden death, suicide).

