## Methods/design

### Study design

A single-case experimental prospective study was designed in alignment with single-case experimental design (SCED) methodology [42]. Within SCED, each individual is his/her own control group based on the first measurement prior to the intervention. The SCED was selected since single-case designs can capitalize on the ability of technology to easily, unobtrusively, and repeatedly assess health-related behavior [43]. The study design is highlighted in Fig. 1. It is based on the Changing Criterion design in which the intervention and delivery of intervention are modified through personalization of (a) goals/tasks and (b) with spoken language interfaces and embodied conversational agents to complement the regular baseline delivery mode via the digital interfaces of the mHealthApp. The study will take place between 1st of May 2021 and 31st of December 2022, with the recruitment period between 1st of April 2021 and 15th May 2021. Data collection is first carried out prior to intervention, during recruitment round (T1). Each recruited individual will sign a letter of consent and fill in CASE-cancer and PAM questionnaires. The SUS questionnaire responses, along with CASE-Cancer and PAM will be collected following a baseline phase (T2) which will last for 6 months. During this phase a ‘generic’ intervention will include a recording of the diary (at least 3 times a week), report regarding their emotional state (at least once a day) and answering a specific PRO for reporting Health Related QoL and symptoms (a different PRO each day). In total, we expect 10–15 min of interaction every day. T2 will conclude with the first follow-up with clinician, during which data regarding primary (CASE-Cancer, PAM, SUS/EUQ) and secondary endpoints will be collected. The personalized intervention phase (T3) will include execution of tasks on mHealth App personalized for the survivor. The data collection tools will remain the same, however the responsible oncologist will define which of the tools the patient must implement (e.g., which PROs) and in what frequency, depending on the risk assessment implemented by the clinical staff. During intervention, specific tools may change depending on the risks detected for the specific patient. T3 concludes with a follow-up during which data regarding primary/secondary endpoints (CASE-Cancer, PAM, SUS/UEQ). A first comparison between generic intervention and personalized intervention will be made. The AI supported clinical intervention (T4) will introduce embodied conversational agent EVA [44] and AI-drive risk assessment engine to deliver fully personalized intervention and to demonstrate that the data-driven models developed within PERSIST can improve quality of life of cancer survivors by acquiring, managing, sharing, and processing big data to create overall actionable insights at the point of care.

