#### Study itinerary

Follow-up data will include updated information on main outcomes (acceptability and usability). Specific questionnaires related with satisfaction and usefulness will be applied to patients and physicians. In addition, healthy habits, disease knowledge, self-management, QoL, and morbidity and mortality end-points will be analyzed.

The recruited patients will receive the necessary devices for the correct development of the follow-up phase of the clinical study: a smartphone and a wearable quantifying device for physical activity estimation and health parameters measurement (such as blood pressure and heart rate). The overall Implementation of the study is visualized in Table 1.

**Table 1 Tab1:** The itinerary of the single-case experimental prospective study

Study procedures	Screening/recruitment	Baseline collections (T1)	Follow up visits		
			Visit 2 (T2)	Visit 3 (T3)	Visit 4 (T4)
Informed consent	X				
Inclusion/exclusion criteria	X				
Questionnaires for Primary and Secondary endpoints		X	X	X	X
Medical history (data collection)		X			
Candidate receives a smartwatch	X				
Candidate receives a smartphone	X				

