#### Statistical analysis

A descriptive analysis of clinical characteristics will be performed. The quantitative parameters will be summarized by its average ± standard deviation and percentiles, while for the qualitative variables the frequencies and percentages will be computed correspondingly.

In order to test the objectives, for CASE-cancer, SUS/UEQ and scores as well as for single items, differences between pre, post, and follow-up measurements will be analyzed by parametric test (Student’s *t*-test/ANOVA), non-parametric test (Wilcoxon signed-rank test) and McNemar test (for categorical measures).

Descriptive statistics of the negative outcomes and/or complications (hospitalization, exacerbations, treatment adherence, depression, reoccurrence and drug escalation) reported in the study will be used. These measures and patient trajectories (appearance of secondary diseases, worsening late toxicities or development of fatal events) will compare with data extracted from retrospective study. We will use univariate tests like Student’s *t*-test and chi-square test and multivariate models. For all the comparisons, sub-analyses will be carried out stratifying by type of cancer, sex and any other variable considered of interest.

An intention-to-treat analysis and sensitivity analysis of observed data will be performed. We will use R 3.4.2 and SPSS version 19 for statistical analysis. Test results with a *p* value below 0.05 will be deemed statistically significant.

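### The protocol's sections disagree on the primary outcome, and the CASE-cancer hypothesis fixes neither the two visits nor the score to be tested, so the 5% level of the headline claim is not secured

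*Protocol article*

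**What the plan says.** The protocol article describes the primary outcome in several places:

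- **Primary and secondary endpoints.** The primary endpoint is "increased perceived self-efficacy in participants (80 colorectal, 80 breast cancer survivors from the 4 pilot hospitals", "as measured using CASE-cancer scale for cancer as the validated standardized measure". The secondary list opens with "observing modifications in patient activation levels measured using the PAM" and continues with SUS and UEQ.
- **Study design.** At the follow-up that closes T2, "data regarding primary (CASE-Cancer, PAM, SUS/EUQ) and secondary endpoints will be collected". Here PAM and SUS/UEQ (printed EUQ) stand inside the primary bracket.
- **Study itinerary.** "Follow-up data will include updated information on main outcomes (acceptability and usability". Self-efficacy is not mentioned in that sentence.
- **Objectives and hypotheses.** "The primary clinical objective is to assess the acceptability and usability of the mHealthApp", together with its effect on self-efficacy and satisfaction with care. The same section then selects CASE-cancer as the measure. It also states "The secondary clinical objectives include measuring the patient activation and acceptance of the mHealthApp", so acceptance appears on the secondary side as well.
- **Outcomes.** The first paragraph gives four batteries, T1 to T4. The second ties the primary outcomes to four batteries labelled pre-screening, T1, T2 and T3.

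The Hypothesis section states one comparison: self-efficacy at the beginning against the end of the intervention. It gives no T-labels. The Statistical analysis section applies t-test/ANOVA, Wilcoxon and McNemar tests to scores and to single items over pre, post and follow-up measurements. It adds open-ended sub-analyses and says that any p "value below 0.05 will be deemed statistically significant".

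**The concern.** A single-group before-and-after study rests its headline claim on one comparison, so that comparison must be identifiable before the data are seen. Here two things are unsettled.

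First, a reader who follows Study design or Study itinerary could present an activation or usability result as a primary finding, while a reader who follows the endpoint list could not.

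Second, even for a reader who keeps strictly to CASE-cancer, several tests fit the hypothesis. The beginning could be T1 or the close of the six-month generic phase at T2, which Study design calls the baseline phase. The end could be T3, which closes the phase named as personalized, or T4. The outcome could be the total score or an item, and the test could be parametric or rank-based.

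If the choice is made after the results are known, a nominal p<0.05 no longer carries a 5% error rate.

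**Working it through.** **1. The endpoint statements side by side**

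| Section | Treated as primary or main | PAM | SUS/UEQ, usability |
|---|---|---|---|
| Primary and secondary endpoints | CASE-cancer | secondary | secondary |
| Study design | CASE-cancer, PAM, SUS/UEQ | primary | primary |
| Study itinerary | acceptability, usability | not named | main |
| Objectives and hypotheses | acceptability, usability, self-efficacy, satisfaction with care; CASE-cancer then chosen | secondary | both |
| Outcomes | batteries at pre-screening, T1, T2, T3 | in the batteries | in the batteries after the first |

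The first three rows cannot all be right.

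**2. Inputs for the error rate**

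- From the documents: N = 160; two-sided 0.05; CASE-cancer at T1, T2, T3 and T4.
- Assumed: no true change; complete data; normal scores; equal variance and equal correlation ρ between any two visits; paired t-tests; any one significant contrast is reported as the primary result.

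**3. The plan's own level.** One contrast, T1 against T4, has an error rate of 0.05 by construction. Simulation at N = 160 (6,000 runs per setting) gave 0.050 to 0.051. The 5% level holds if one contrast is fixed.

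**4. Correlation between contrasts against T1**

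- Var(Yj − Y1) = 2σ²(1 − ρ)
- Cov(Yj − Y1, Yk − Y1) = σ²(1 − ρ)
- Correlation = 1/2, whatever ρ is

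Under the equal-correlation assumption, the results below therefore do not depend on the value of ρ.

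**5. Any of k contrasts against T1.** With c = 1.96 and normal approximation,

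P = 1 − ∫ φ(x) [Φ((c − x√½)/√½) − Φ((−c − x√½)/√½)]^k dx

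- k = 2 (T3 or T4 against T1): P = 0.091. Independent tests would give 1 − 0.95² = 0.098.
- k = 3 (T2, T3 or T4 against T1): P = 0.125. Simulations at N = 160 gave 0.123 to 0.137. Independent tests would give 1 − 0.95³ = 0.143.

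**6. Any of the six visit pairs.** At least one pair is significant when the range of four standard normal values exceeds 1.96 × √2 = 2.77. P = 0.203. Simulations gave 0.200 to 0.214. Independent tests would give 1 − 0.95⁶ = 0.265.

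**7. Not quantified.** Single items, the choice between t-test and Wilcoxon, and sub-analyses would add to these rates. The article does not give the number of items tested or their correlations, so no figure is offered.

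**The case against.** The strongest reply is that the formal definition is clear. The Hypothesis section and the endpoint list confine the claim to self-efficacy on CASE-cancer, beginning against end. This stands. A reader might infer that the hypothesis could be declared met by any of many tests, including one on PAM or SUS, with an error rate of 40 to 50%. The documents do not support that:

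- A PAM or SUS result cannot meet a self-efficacy hypothesis.
- The sentence listing the tests does not name PAM, although a word may have been lost there.
- Counting all six visit pairs for usability would need a SUS/UEQ measurement at T1, and none is planned.
- No rule says that any one success counts.

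The conflicting sections can also be read more mildly. The Study design bracket sits in a data-collection sentence, and for later visits the text writes primary and secondary together, which suggests a loose list of instruments. Objectives and hypotheses goes on to choose CASE-cancer. The odd labels in Outcomes may be the same four occasions under shifted names. An ANOVA across visits would be one omnibus test rather than six pairwise ones. These points weaken the conflict but do not remove it: the Study design bracket and the itinerary's main outcomes still contradict the endpoint list and need correcting.

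Finally, a multiplicity adjustment may sit in an analysis plan that is not shown, and the study calls itself mainly a pilot. Its absence from the article is therefore not held against it. The point rests on contradictory text and on a stated significance rule that covers scores and items alike.

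**Conclusion.** The concern holds in a limited form. The sections contradict one another on what is primary. The one formal hypothesis is restricted to CASE-cancer, but its two time points are unlabelled. T1 is the likelier starting point, because the abstract's Discussion compares with recruitment. The end is less clear: the hypothesis speaks of the personalized intervention, which fits T3, while Study design has a later final follow-up, which fits T4.

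If whichever CASE-cancer contrast succeeds may be reported as primary, the false-positive rate is about 9% on the narrowest reading, 13% for three contrasts against T1, and 20 to 21% for all six pairs. These sizes depend on that reporting rule and on equal between-visit correlations; they are not error rates that the protocol itself implies. If one total-score contrast is fixed in advance, the rate is 5%.

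**What to change.** Name one primary test in the endpoint section: change in CASE-cancer total score from T1 to T4, with one named paired test at two-sided 5%. Then reconcile the other sections with it:

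- **Study design and Study itinerary:** move PAM, SUS/UEQ, acceptability and usability to secondary.
- **Objectives and hypotheses:** align the primary objective with self-efficacy. Take satisfaction with care out of it, since no pre-intervention measurement is stated and the satisfaction items in Outcomes concern the intervention and system at T2 and T3.
- **Outcomes:** use one set of visit labels and include T4.
- **Statistical analysis:** label the T2 and T3 contrasts secondary, and single items and sub-analyses exploratory, so that the 0.05 rule supports a confirmatory claim for the primary test only.

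Whether to adjust across secondary outcomes, for example by Holm, is optional and can be left to the analysis plan.

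The cost is wording and fewer results that can be called significant. No new data are needed. Fixing one test is also cheaper than adjusting: at the plan's d = 0.25 and N = 160, a single test at 0.05 has 88.2% power, against 77.0% if three contrasts against T1 were kept with Bonferroni at 0.05/3 = 0.0167.

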
**Fig. 1 Fig1:**
[figure not shown]
The design of the single-case experimental prospective study

During the final follow-up, the data regarding the primary/secondary endpoints will be collected. To measure the overall impact of the digital intervention we will adapt the Model for the Assessment of Telemedicine (MAST) methodology [45]. The patient domain will be assessed through CASE-cancer, PAM, SUS, UEQ. The clinical relevance will be assessed by: (i) analyzing the impact of Big Data prediction models to support decision-making in patient follow-up, and (ii) the impact of the intervention on against the appearance of secondary diseases, worsening late toxicities or development of fatal events (sudden death, suicide).

#### Study setting

The study will involve 160 survivors (80 survivors of Breast Cancer and 80 survivors of Colorectal Cancer) from four countries, Belgium, Latvia, Slovenia, and Spain. Each of the sites will recruit 40 cancer survivors according to the inclusion/exclusion criteria. Study will involve the use of digital intervention during every-day activities outside the clinical environment (i.e., at the subjects’ homes). The data collected will be evaluated during regular 6 month follow ups.

#### Study itinerary

Follow-up data will include updated information on main outcomes (acceptability and usability). Specific questionnaires related with satisfaction and usefulness will be applied to patients and physicians. In addition, healthy habits, disease knowledge, self-management, QoL, and morbidity and mortality end-points will be analyzed.

The recruited patients will receive the necessary devices for the correct development of the follow-up phase of the clinical study: a smartphone and a wearable quantifying device for physical activity estimation and health parameters measurement (such as blood pressure and heart rate). The overall Implementation of the study is visualized in Table 1.

**Table 1 Tab1:** The itinerary of the single-case experimental prospective study

Study procedures	Screening/recruitment	Baseline collections (T1)	Follow up visits		
			Visit 2 (T2)	Visit 3 (T3)	Visit 4 (T4)
Informed consent	X				
Inclusion/exclusion criteria	X				
Questionnaires for Primary and Secondary endpoints		X	X	X	X
Medical history (data collection)		X			
Candidate receives a smartwatch	X				
Candidate receives a smartphone	X				

### Participants and recruitment

A 3-month period of recruitment is initially estimated, with 1 month of active enrolment. Before the enrolment, the first 2 months of the period will include a medical evaluation. This will confirm the curative cancer treatment process and verify that the patient meets all inclusion criteria but none of the exclusion ones. During recruitment, we will also provide further information about the study to eligible patients and give them the informative brochure and the informed consent form to sign.

#### Patient information and informed consent

Clinical partners will develop an informed consent document translated in their local language and will apply for their local or national bioethics committee approval. GDPR regulation will be strictly followed to protect personal data of participants. Each center will be responsible to obtain a signed informed consent from the patient before inclusion in the study. The participants will be recruited by 4 hospitals involved in the study from different EU countries (Belgium, Latvia, Slovenia and Spain). Every clinical partner will involve 40 survivors, 20 patients from C18/C19 (Colorectal cancer) and 20 patients from C50 (breast cancer). In total 160 patients will be recruited to participate in envisioned two-phases clinical study. The recruitment stage will begin in April, 2021. The study will involve breast and colorectal cancer patients who have survived beyond curative cancer treatment. We will consider a survivor patient all breast and colorectal cancer patients who survive without recurrence beyond 3–24 months after the end of treatment (surgery ± radiation therapy ± chemotherapy), they have received. For colorectal cancer survivors' group, two subgroups will be included (chemotherapy and non-chemotherapy). None of the groups will be lower than 33% in ratio to the other. For breast cancer survivorspatients that have had surgery and patients that have had chemotherapy.

#### Inclusion criteria

≥ 18 and ≤ 75 years at the moment of recruitment; stable clinical situation, life expectancy of more than 2 years according to researcher opinion; ability to understand study instructions, fulfil follow-up visits and sign informed consent; sufficient level of technology literacy enabling the patient to manage mobile terminals (smartphones, smartphone apps, tablets); good internet connection in his/her place of residence or mobile data-plan.

